#### Inclusion criteria

2.4.1

- Adult aged 20 to 75 years.- Subacute hemiparesis (< 6 months).- BMI between 18.5 and 25.- Written consent to participate in the study.

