### Study design

2.2

This study will be conducted in strict adherence to the Consolidated Standards of Reporting Trials (CONSORT) guidelines, and will employ a single-blinded, controlled, randomized design, wherein participants will be randomly assigned to one of two groups: the conventional therapy group (CTG) or the Eccentric training group (ETG). Both groups will undergo a series of assessments at: Ji (initial assessment) and Jf (final assessment) as illustrated in Figure 1. The study will begin with a recruitment phase, followed by a screening phase. Subsequently, there will be a 4-week period allocated for experimental testing before the intervention, and an additional 4 weeks for experimental testing after the intervention. The experimental testing will include clinical health assessments, biomechanical assessments, neuromuscular evaluations, and functional assessments.

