### Randomization

2.3

The random assignment of participants to their respective groups will take place on the day they will be included in the study and will be supervised by the investigator. The randomization list will be created by an independent statistician from the clinical research unit. For the randomization process, a computer-generated list will be generated using the Clinical Trial Randomization Tool. This list will then be uploaded into an online case report form. Each study participant will be assigned a unique allocation study number in a sequential format (TMP00X). The rigorous blinding will be maintained until the database will be finalized. A blinded assessor will conduct three visits: one before, one in the middle, and one after the interventions, while unblinded kinesiologists, who provide treatment and exercise sessions, will not be involved in the assessment sessions. All required information stipulated by the study protocol will be entered diligently into the Electronic Data Capture system in real-time as it will be acquired.

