### Recruitment

2.4

Participants will be recruited from the clinic of Parc de Belleville in Paris between the 1st of January 2024 to 31st May 2024. Recruitment will be accomplished by disseminating study participation offers in clinical centers, and subsequently, the medical staff will compile a list of volunteers to the experimenter. To participate in this study, subjects will be invited for an admission consultation (Pre-inclusion) (J0) with the principal investigator. Before this consultation, the investigator will need to ensure that the patient meets the study’s inclusion and exclusion criteria.

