#### Conventional therapy

2.5.1

The conventional therapy program will extend over a period of 12 weeks, consisting of a total of 36 sessions with three sessions per week conducted by physiotherapists. The program will include both isometric and concentric strengthening exercises specifically targeting the plantar flexors. The load and intensity of these exercises will be individualized according to each participant’s capabilities. The conventional therapy will consist of:

- Isometric Exercises: Participants will perform isometric contractions at 70% of their MVC for 10 s, followed by a 20 s rest interval. This cycle will be repeated in sets of 10.- Concentric Exercises: These exercises will involve the use of weights or resistance bands. The intensity of these exercises will progressively increase from 50 to 80% of the MVC over the course of the program. The number of repetitions per set will also gradually increase from 8 to 12, with each exercise being performed in three sets.- Stretching Sessions: The program will incorporate stretching exercises for the plantar flexors, performed both passively and actively. Each stretch will be held for 30 s and repeated three times for each target muscle.

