*Name:* The ET protocol.*Why:* The ET protocol will aim to enhance walking capacity and reduce spasticity.*What (Materials):* The eccentric exercise program will be carried out using the BIODEX isokinetic device (Biodex 4 Medical Systems, Inc., Shirley, NY, USA).*What (Procedures):* The eccentric program will last for 12 weeks, with a frequency of 3 sessions per week, totaling 36 sessions. At least 1 day of rest will be required between two training sessions. The participants will be placed in the similar position of the neuromuscular assessments (reference position). The Biodex System 4 dynamometer settings for the exercise sessions will be conducted under settings like those used for the assessments. The training program will be divided into two phases: a familiarization phase and a progression phase. Training will be progressing according to the schedule presented in the Figure 2. The familiarization phase, involving the manipulation of three key variables, will aim to reduce risks and enhance the advantages of eccentric strength training. This phase will unfold in two stages (33). The first stage will consist of two sessions designed to familiarize participants with the muscle recruitment patterns associated with isokinetic eccentric exercises. The second stage will span a one-week preparation period, intended to elicit a protective muscular response, and progressively condition the muscles for higher eccentric intensities (33). For the progression phase, a triangular pyramid training paradigm will be employed (28). The rationale will be to, first, train to increase the speed at which force can be produced and second increase the load produced during dynamic contractions. Custom-designed attachments will be used to enable optimal biomechanical alignment for proper performance of the ankle joint movement (28). Participants will be instructed to “resist and try to stop the dynamometer.” Verbal encouragement will continue to be provided throughout the training sessions to motivate maximal effort. This form of training will conceptually remain like power training, which involves rapid muscle contractions. Power training will continue to be considered a safe but intense form of training that is more effective than traditional resistance training using slower contractions.*Who:* By a kinesiologists specialized in adapted physical activity.*How:* Face to face sessions.*Where:* Rehabilitation department.*When and how much:* the ET protocol begins the 1st of January 2024 and concludes on the 31^st of^ May 2024. Each week will include three sessions, making a cumulative total of 36 sessions. Each session lasts 45 min, with a 15-min warm-up and 30 min of actual exercise.*Tailoring:* The determination of the number of sets will be tailored to the patient’s abilities.*Modifications:* Modifications will be implemented to the protocol in each session, involving adjustments such as an increase in the number of sets or repetitions.*How well (planned):* The training program will be divided into two phases: a familiarization phase and a progression phase. Training will be progressing according to the schedule presented in the Figure 2. The program’s progression will be determined by two factors: a quantitative element linked to the training load (volume/intensity) and a qualitative aspect associated with the nature of the exercises (eccentric exercise).*How well (actual):* Not started yet.

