Walking performance is influenced by lower-extremity muscle strength (28). Particularly, the PF are pivotal in the walking process, serving as agonists and contributing to concentric activity that significantly impacts the quality of propulsion during walking (52). However, the effect of ET interventions on walking function in individuals with spastic paresis has produced mixed results in prior studies. While some investigations have reported significant improvements in walking speed and function (53, 54), others have not observed significant enhancements (55). This variability in outcomes may be attributed to the timing of intervention, as some studies were conducted during the chronic phase, typically after six months post-injury, when spasticity may have become fully established. This study seeks to address this potential limitation by implementing the intervention during the sub-acute phase. Furthermore, other factors such as the intensity of eccentric exercise, its duration, and the overall methodology of intervention may also play a role in these divergent findings, warranting further investigation.

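### The six-month limit applies at inclusion, but up to 16 weeks of testing and training follow, so part of an intervention described as sub-acute can fall after six months

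*Protocol article*

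**What the plan says.** Section 2.4.1 (Inclusion criteria) limits time since onset once: "Subacute hemiparesis (< 6 months". Three sections fix when that limit is applied and what follows.

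- **Eligibility check.** Section 2.4 (Recruitment) places it ahead of the J0 visit: "Before this consultation, the investigator will need to ensure that the patient meets the study" (the sentence goes on to name the entry criteria). Section 2.3 (Randomization) says allocation "will take place on the day they will be included in the study".
- **Testing before training.** Section 2.2 (Study design): "there will be a 4-week period allocated for experimental testing before the intervention".
- **Training.** Section 2.5.1: "The conventional therapy program will extend over a period of 12 weeks". Section 2.5.2: "The eccentric program will last for 12 weeks, with a frequency of 3 sessions per week, totaling 36 sessions".

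Section 3 (Discussion) offers timing as a possible reason for mixed walking results in earlier work: "some studies were conducted during the chronic phase, typically after six months post-injury, when spasticity may have become fully established". It continues: "This study seeks to address this potential limitation by implementing the intervention during the sub-acute phase". No section requires training to start or end within six months of the stroke.

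**The concern.** The eligibility rule describes the patient on the day of entry. The Discussion describes when the intervention is given. Between the two lie up to 4 weeks of testing and 12 weeks of training, which together are long compared with a six-month window. A patient can satisfy the entry rule and still receive most or all training in the period that the Discussion calls chronic.

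What is at stake is whom the result describes. The abstract and conclusion present the trial as evidence on eccentric training in sub-acute stroke. If an unknown share of the training is given after six months, that label is not secured by the design, and readers cannot judge how far it applies.

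**Working it through.** The article gives no figure on this point to reproduce, so the check is timeline arithmetic.

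**Inputs**
- Entry limit L: six months (section 2.4.1), taken as 26 weeks.
- Delay d from inclusion to first session: 0 to 4 weeks. Section 2.2 allocates 4 weeks to testing. Section 2.4.2 puts the initial evaluation on the day of admission, so the delay may be shorter.
- Training length: 12 weeks in both arms (sections 2.5.1 and 2.5.2).
- Start of the chronic phase: after six months (section 3), so also 26 weeks.

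**Formulas.** For a patient included t weeks after onset, training runs from t + d to t + d + 12. The number of training weeks after six months is t + d + 12 − 26, bounded below by 0 and above by 12.

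**Thresholds (no distribution needed)**
- All training within six months requires t ≤ 26 − 12 − d: week 14 if d = 0, week 10 if d = 4.
- At least half of training after six months from t = 26 − 6 − d: week 20 if d = 0, week 16 if d = 4.
- All training after six months from t = 26 − d: week 22 if d = 4. If d = 0 this is reached only at the limit itself.

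**Example, t = 25**
- d = 0: training runs from week 25 to week 37, with 25 + 0 + 12 − 26 = 11 of 12 weeks after six months.
- d = 4: training runs from week 29 to week 41, with all 12 weeks after six months.

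**Illustration, assuming inclusion uniform over 0 to 26 weeks**

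| Quantity | d = 0 | d = 4 |
|---|---|---|
| Finish training after six months | 12/26 = 46% | 16/26 = 62% |
| Start training after six months | 0% | 4/26 = 15% |
| Mean share of training time after six months | (12 × 0.5)/26 = 23% | (4 × 1 + 12 × 0.5)/26 = 38% |

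**Sensitivity**
- With six months taken as 24 weeks, the share finishing late is 12/24 = 50% (d = 0) to 16/24 = 67% (d = 4).
- With a 26-week limit but no one included before week 4, it is 12/22 = 55% to 16/22 = 73%. An unstated lower limit would therefore raise the share, not lower it.
- With no assumption about the distribution, the share finishing late can be anything from 0% (everyone included by week 10) to 100% (everyone included after week 14).

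**After moving the limit to the first session, same uniform assumption**
- d = 0: starts span weeks 0 to 26, as before. 12/26 = 46% finish late, and 6/26 = 23% of training time is late.
- d = 4: inclusion spans weeks 0 to 22. 12/22 = 55% finish late, and 6/22 = 27% of training time is late.
- In both cases nobody starts after six months.

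**The case against.** The strongest reply is that classifying stroke phase at enrolment is a defensible choice and that giving the intervention in the sub-acute phase can be read as starting it then. On that reading the mismatch shrinks to a delay of at most 4 weeks, and moving the limit to the first session still leaves 23% to 27% of training time after six months. That stands in part: the eligibility change alone is not a cure, which is why the wording of the conclusion must change too. It does not remove the point, because the entry rule as written does not guarantee even a start within six months.

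It is also fair that the percentages rest on an assumed distribution, and that training wholly after six months needs some testing delay. The thresholds and the week-25 example need no distribution, and with no delay 11 of 12 weeks still fall late.

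A reader might infer more than the article supports:

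- **That the trial can no longer test whether timing explains earlier mixed results.** It could not do so under any entry rule, because it has no chronic-phase comparison group. Neither stated objective in section 1 concerns timing.
- **That there is definitely no lower limit.** The word subacute is itself part of the criterion, although no number is attached to it.
- **That the lack of described stratification is an error.** An article may leave strata to the full protocol.

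The recruitment and training dates do not help the plan here, since they bound calendar time and not time since stroke.

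**Conclusion.** The point holds as a mismatch between the entry rule and the stated timing of the intervention. Patients included after about week 14 (no delay) or week 10 (full delay) receive part of their training after six months, and those included near the limit receive nearly all of it then. This follows from the article's own durations, with six months taken as 26 weeks. The proportion of patients affected cannot be known from the article. The 46% to 62% finishing late and the 0% to 15% starting late are illustrations under uniform inclusion.

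A reader might take this as a bias between arms. The article does not support that: both arms share the entry rule and the training length, so the randomised comparison is not biased by it. The consequence is for the target population and for the sub-acute label on the conclusion. It merits a change because the remedy is small and alters both who is trained and what can be claimed.

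**What to change.** Reconcile sections 2.2, 2.4.1 and 3 in three steps.

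1. **Eligibility.** Apply the limit to the first planned training session: less than six months from stroke onset to that session.
2. **Data and analysis.** Record days from stroke onset to the first session. In the between-arm gait-speed comparison, replace the unadjusted independent t-test of section 2.8 with a linear model containing arm and this covariate. Because the session follows randomisation, fix its planned date before allocation is known and use that date for the covariate; report the actual date descriptively.
3. **Conclusion.** State that training was started in the sub-acute phase, and report how much training fell after six months. Even with step 1, about 23% to 27% of training time would do so under the uniform assumption.

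The cost of step 1 is that up to the last 4 weeks of the inclusion window become ineligible. Step 2 needs one date that must be known anyway to check eligibility, one model parameter, and software that fits a linear model. Step 3 is wording only. If enrolment is already complete, the descriptive part of step 2 and step 3 remain possible, and the adjustment can use time from onset to inclusion.

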#### Exclusion criteria

2.4.2

- Ankle impairment- Botulinum toxin injections in PF within the last 4 months before study inclusion to ensure that the muscle properties were not influenced by the toxin’s effects.- Medical contraindication for maximal effort.- Neurodegenerative disorders.- Cardiovascular disorders.- History of epilepsy.

The investigator will explain the purpose of the study, and the experimental protocol. The patient will then be given time for consideration. If they will agree, on the day of admission, they will sign an informed written consent to participate in the study, and then they will undergo their initial evaluation (Ji).

### Intervention

2.5

#### Conventional therapy

2.5.1

The conventional therapy program will extend over a period of 12 weeks, consisting of a total of 36 sessions with three sessions per week conducted by physiotherapists. The program will include both isometric and concentric strengthening exercises specifically targeting the plantar flexors. The load and intensity of these exercises will be individualized according to each participant’s capabilities. The conventional therapy will consist of:

- Isometric Exercises: Participants will perform isometric contractions at 70% of their MVC for 10 s, followed by a 20 s rest interval. This cycle will be repeated in sets of 10.- Concentric Exercises: These exercises will involve the use of weights or resistance bands. The intensity of these exercises will progressively increase from 50 to 80% of the MVC over the course of the program. The number of repetitions per set will also gradually increase from 8 to 12, with each exercise being performed in three sets.- Stretching Sessions: The program will incorporate stretching exercises for the plantar flexors, performed both passively and actively. Each stretch will be held for 30 s and repeated three times for each target muscle.

#### Eccentric training protocol

2.5.2

In the absence of a standardized eccentric isokinetic training protocol established for hemiparetic subjects on the plantar flexor muscles, the protocol designed for this study drew inspiration from the one established by Clark and Patten (28) and by Harris-Love et al. (33). This protocol will allow the introduction of eccentric stimulus to individuals who are new to this type of training. It will progressively advance their program to include workload levels that are sufficient to stimulate muscular plasticity optimally, thereby inducing skeletal muscle adaptations. The ET protocol will adhere to guidelines provided by the TiDieR, which encompass the following 12 items:

*Name:* The ET protocol.*Why:* The ET protocol will aim to enhance walking capacity and reduce spasticity.*What (Materials):* The eccentric exercise program will be carried out using the BIODEX isokinetic device (Biodex 4 Medical Systems, Inc., Shirley, NY, USA).*What (Procedures):* The eccentric program will last for 12 weeks, with a frequency of 3 sessions per week, totaling 36 sessions. At least 1 day of rest will be required between two training sessions. The participants will be placed in the similar position of the neuromuscular assessments (reference position). The Biodex System 4 dynamometer settings for the exercise sessions will be conducted under settings like those used for the assessments. The training program will be divided into two phases: a familiarization phase and a progression phase. Training will be progressing according to the schedule presented in the Figure 2. The familiarization phase, involving the manipulation of three key variables, will aim to reduce risks and enhance the advantages of eccentric strength training. This phase will unfold in two stages (33). The first stage will consist of two sessions designed to familiarize participants with the muscle recruitment patterns associated with isokinetic eccentric exercises. The second stage will span a one-week preparation period, intended to elicit a protective muscular response, and progressively condition the muscles for higher eccentric intensities (33). For the progression phase, a triangular pyramid training paradigm will be employed (28). The rationale will be to, first, train to increase the speed at which force can be produced and second increase the load produced during dynamic contractions. Custom-designed attachments will be used to enable optimal biomechanical alignment for proper performance of the ankle joint movement (28). Participants will be instructed to “resist and try to stop the dynamometer.” Verbal encouragement will continue to be provided throughout the training sessions to motivate maximal effort. This form of training will conceptually remain like power training, which involves rapid muscle contractions. Power training will continue to be considered a safe but intense form of training that is more effective than traditional resistance training using slower contractions.*Who:* By a kinesiologists specialized in adapted physical activity.*How:* Face to face sessions.*Where:* Rehabilitation department.*When and how much:* the ET protocol begins the 1st of January 2024 and concludes on the 31^st of^ May 2024. Each week will include three sessions, making a cumulative total of 36 sessions. Each session lasts 45 min, with a 15-min warm-up and 30 min of actual exercise.*Tailoring:* The determination of the number of sets will be tailored to the patient’s abilities.*Modifications:* Modifications will be implemented to the protocol in each session, involving adjustments such as an increase in the number of sets or repetitions.*How well (planned):* The training program will be divided into two phases: a familiarization phase and a progression phase. Training will be progressing according to the schedule presented in the Figure 2. The program’s progression will be determined by two factors: a quantitative element linked to the training load (volume/intensity) and a qualitative aspect associated with the nature of the exercises (eccentric exercise).*How well (actual):* Not started yet.

**Figure 2 fig2:**
[figure not shown]
The progression of eccentric training protocol.

### Outcome measures

2.6

#### Functional parameters

2.6.1

First, gait speed (m/s) will be measured through the 10-meter walking test. Secondly, the maximal range of motion (ROM), defined as the extent of stretch that the participant can comfortably endure during the stretching maneuver, will be measured using the BIODEX isokinetic device (Biodex 4 Medical Systems, Inc., Shirley, NY, United States). Participants will be positioned prone on the isokinetic machine and instructed to achieve complete relaxation. To minimize the involvement of unrecorded muscles, the ankle will be securely fixed in a relaxed position on the isokinetic dynamometer. Starting from the neutral position (0°), the ankle joint will be passively mobilized from plantar to dorsiflexion at a slow angular velocity (2°/s). Participants will be encouraged to maintain a state of relaxation and halt ankle rotation when they will perceive a tolerable maximum stretch. Then, the ROM (°) will be recorded for each participant.

